### Recruitment {15}

Participants are recruited through a variety of strategies such as referrals, registries, community events, study flyer distributions, support groups, presentations, exhibits, social media, and newspaper advertisement. We also recruit a general population by leveraging our extensive network with organizations and expand new partnerships through a confianza triangle, where research teams and our community partners, such as promotores (community health workers). We forge connections to participants by establishing trust with organizations that the community also trusts, thus strengthening our referral stream.

## Assignment of interventions: allocation

### Sequence generation {16a}

Prior to recruitment, the statistician created 2 randomization schedules using random permuted blocks of 3 and 6 participants in the study’s Research Electronic Data Capture (REDCap) system.

### Concealment mechanism {16b}

The REDCap randomization modules are only accessible to designated staff such as the study coordinator and interventionist to reveal group assignment.

### Implementation {16c}

The study statistician generated the allocation sequence. The study coordinator and project manager enroll participants. The study coordinator or her designated interventionist assigns participants to interventions.

## Assignment of interventions: blinding

### Who will be blinded {17a}

All investigators (except for the statistician) and outcome data collectors are blinded after assignment to interventions. They do not have access to REDCap randomization modules. Group allocations are concealed to the investigators during trial implementation. Once participants are enrolled, the data collectors only interact with participants for data collections.

### Procedure for unblinding if needed {17b}

The study interventionists and the participants are not blinded. Unblinding to investigators (except for the statistician) and data collectors is not permissible during the trial.

## Data collection and management

### Plans for assessment and collection of outcomes {18a}

All staff are required to complete the onboarding, semi-annual and booster training until they are 100% compliant with the study protocol. Intervention delivery is entered into the REDCap database in real time. Outcomes are collected with paper and pencil and are double checked for completeness, accuracy, and data entry.

### Plans to promote participant retention and complete follow-up {18b}

We proactively identify potential dropouts and missed visits to address them promptly. If a participant passes away, we will follow up with study partners regarding the circumstance of death. If a participant intends to withdraw, we will respect the participant’s choice. All attempts will be made to collect data to allow for inclusion in the analysis and reasons for withdrawal will be recorded. If staff non-compliance is found, particularly when non-compliance results in retention or follow-up issues, the study coordinator will notify the PI immediately and staff re-training will be performed within a week to avoid repeating the problem. Any missing data will be assigned to a data collector for collection. We will track and analyze dropouts, missed visits, and loss to follow-up for the overall sample and across groups and consider them as potential covariates in analyses.

### Data management {19}

The PI is responsible for the integrity and validity of the study data. The PI and the study coordinator oversee all participant records, adherence to the protocol by all staff, screening and recruitment logs, percent of exercise sessions attended, missed sessions, compliance, retention, adverse events, and study outcomes, and ensure data creation, completeness, quality check, and audits. The PI and statistician develop and implement a data audit and edit plan to ensure data accuracy and completeness.

We collect data primarily electronically using a de-identified REDCap study database via a secure web interface. Data collected on paper will be manually entered into the REDCap database. Data collected on paper will be double checked for accuracy, completeness, and data entry accuracy by the staff and research assistants (RAs) who collected data and by another staff or RA. The web server of REDCap database is housed on secure servers operated by Arizona State University and are backed up regularly. Access to the system by username and password requires specific permission from the PI.

### Confidentiality {27}

All paper and electronic forms will be identified with a unique ID number only to protect participants’ and study partners’ privacy. Paper copies of data will be stored in a dedicated office space and kept in locked file cabinets with limited access. The linkage between the participant’s name and the screening ID will be kept separately and accessible by study staff involved in the screening process and blinded to all investigators. The study coordinator and interventionists will have access to HIPAA data to ensure participant safety and care coordination in case of adverse events (AEs). Screening IDs are first assigned during screening. Study IDs are assigned to those enrolled in the study. The link between participants’ names and screening/study IDs will be accessible only to the study staff participating in the screening process to allow the transfer of screening information into the study database.

### Plans for collection, laboratory evaluation, and storage of biological specimens for genetic or molecular analysis in this trial/future use {33}

Plasma biomarker specimens are stored on wet ice until the lab technician of Clinical Research Services processes and aliquots them. Aliquoted samples are stored in a − 80 °C freezer. The Clinical Research Services staff handle the collection, processing, and storage of blood specimen. Specimen are transported accordance with the institutional standards of practice. The specimens will be stored beyond their use to satisfy the objectives of the trial and be available to other researchers after the trial via a data sharing agreement.

## Statistical methods

### Statistical methods for primary and secondary outcomes {20a}

In the preliminary analyses, univariate (e.g., means, SDs, frequencies) and bivariate (e.g., ANOVA/Kruskal–Wallis, chi-square, correlation) statistics and plots will be used first to examine distributions of and associations among study variables; to identify potential multivariate outliers, influential cases, and implausible values; to explore missing-data patterns; and to check for systematic between-group differences at baseline. To further investigate if model assumptions are met, preliminary linear-regression models predicting 6-month outcomes from group assignment will be estimated; results will inform the choice of link function (e.g., natural log), error distribution (e.g., negative binomial), and/or data transformation. The internal consistency of each multi-item composite measure will be evaluated. Analyses and plotting will be conducted in R 4.1, SAS 9.4 (Aims I–II), and Mplus 8.7 (Aim III). Holm’s approach [52] and fixed-sequence testing procedures [52–54] will be used to control for an overall false discovery rate across multiple tests.

To address H1a, we will estimate between-group differences in aerobic fitness or WMHv change from baseline to 6 months and baseline to 12 months using an ANCOVA-type approach, a generalized linear model (GLM) in which the randomized group (e.g., MICT vs. control) predicts aerobic fitness or WMH volume at 6 months (or 12 months), adjusting for baseline aerobic fitness or WMHv and potentially relevant covariates and confounders identified in preliminary analyses. To address H1b, we will estimate GLMs paralleling those used to address H1a, but with memory, QoL, physical function, BPSD, and caregiver burden as outcomes. We will also perform similar analyses for exploratory outcomes (Table 2).

To address H2a, we will estimate contrasts corresponding to a monotonic ordering of the means [55] in which mean aerobic fitness at 6 months is the highest in the MICT + HIIT group, followed by MICT + CARE, then MICT only, and then stretching. Unlike a typical linear trend analysis, this approach does not require that the conditions (groups) represent equally spaced intervals along a quantitative continuum (e.g., min/day aerobic exercise).

To address H2b, we will estimate a multivariable logistic regression predicting 6-month responses (non-responder vs. responder) from the R2 group assignment (MICT + HIIT vs. MICT + CARE), adjusting for 3-month VO_2peak_.

To address H3, we will first estimate direct effects of condition initially randomized to group (**X**: a dichotomous indicator of MICT vs. control) on each 6- and 12-month outcome (**Y**: memory). Next, we will estimate indirect (mediated) effects of group (**X**) on memory (**Y**) via one or more 6- or 12-month measure(s) of potential mediators (**M**: e.g., plasma Aβ_42/40_) with structural equation path models using approaches described and implemented by Imai et al. [56], VanderWeele [57], and Muthén et al. [58, 59]. Where warranted, we will adjust estimates of indirect effects for covariates and for X × M interaction effects on outcomes. We will conduct sensitivity analyses to evaluate assumptions about these potential confounders [56]. We will also estimate magnitudes of indirect effects [60].

All analyses will follow the intention-to-treat (ITT) approach to provide unbiased tests of treatment effects. The ITT population will be defined as all randomized participants. We will first examine associations between baseline covariates and missingness in outcomes. Along with dropout records, findings will inform model development to generate multiple complete datasets and, where warranted, the construction of analytic models applied to these datasets, under the assumption that data are missing at random. Imputed datasets will be analyzed separately, and the results pooled to yield estimates of model parameters and associated standard errors. Diagnostic analyses and plots will be used to assess the quality of the imputations [61] and the possibility that data may be missing not at random. Sensitivity analyses based on pattern mixture models with varying assumptions regarding effects of potential missing data on outcome values (e.g., shifts in means) will be used to examine robustness of findings based on missing-at-random assumptions.

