### Objectives {7}

The purpose of this manuscript is to describe the study protocol for FIT-AD SMART, which aims to test the effects and mechanisms of 6-month aerobic exercise that is tailored on aerobic fitness response to MICT in community-dwelling older adults with early symptomatic AD. FIT-AD refers to Function Improvement through aerobic exercise Training in older adults with AD and SMART refers to Sequential, Multiple Assignment, Randomized Trial design. The FIT-AD SMART was built on findings from the FIT-AD Trial that showed individual differences in aerobic fitness responses to MICT to:Aim I. Test the effects of aerobic exercise on aerobic fitness, white matter hyperintensity (WMHv), and patient-centered outcomes in older adults with early symptomatic AD. H1a: Aerobic exercise (MICT, MICT + HIIT, MICT + CARE) will increase aerobic fitness and reduce WMHv over 6 and 12 months more than stretching. H1b: Aerobic exercise will improve patient-centered outcomes over 12 months in comparison to stretching.Aim II. Determine the best exercise to improve aerobic fitness and reduce aerobic fitness non-responses over 6 months in older adults with early symptomatic AD. H2a: MICT + HIIT improves aerobic fitness the most, followed by MICT + CARE, then MICT only, and then stretching. H2b: HIIT reduces the number of MICT non-responders more than CARE.Aim III. Examine the mechanisms of aerobic exercise’s action on memory in early symptomatic AD. H3: Changes in plasma Aβ_42/40_, phospho-tau181 (ptau181), total tau (t-tau), and neurofilament light chain (NfL) mediate memory responses to exercise.

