### Trial design {8}

FIT-AD SMART is a single-site Stage II (according to the NIH Stage Model) sequential, multiple assessment, randomized trial. One hundred and eight (*n* = 108) of community-dwelling older adults with early symptomatic AD are randomized using a 2:1 allocation ratio (randomization 1) to 3-month MICT or 6-month stretching control, after baseline data collection. Their primary family caregivers are also enrolled as study partners. VO_2peak_ is re-assessed at the end of 3 months and is used to identify non-responders (defined in the Methods section) in participants assigned to the MICT group. Non-responders are subsequently re-randomized on a 1:1 allocation ratio to either HIIT or CARE for 3 months (randomization 2). Responders continue MICT for another 3 months (Fig. 1). Both randomizations are stratified by baseline age (66–75, 76–85, 85 + years) using random permuted blocks of 3 and 6. Study outcomes are assessed at 0, 3, 6, 9, and 12 months by trained data collectors who are blinded to group allocation.

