### Criteria for discontinuing or modifying allocated interventions {11b}

After 3 months of MICT, aerobic fitness non-response is determined in a three-hierarchical order as (1) < 5% increase in VO_2peak_ if peak cycle-ergometer exercise test with indirect calorimetry is completed at sufficient effort (e.g., respiratory exchange ratio ≥ 1.0 or HR ≥ 85% of the age-predicted max HR). (2) If exercise test is refused (e.g., participant wishes not to wear testing mask), non-response is indicated by < 10% increase in peak aerobic power (peak watts/kg) on the exercise test. (3) For participants who do not complete the exercise test, non-response is indicated by < 36.5-m increase in the distance of shuttle walk test (SWT). Non-responders are re-randomized 1:1 to HIIT or CARE for 3 months, stratefied by baseline age and random permuted blocks of 3 and 6. Responders continue MICT for 3 more months.

HIIT. An evidence-based “Scandinavian-style” HIIT protocol is used [22, 23]. This protocol includes 40 min of HITT comprising 5 sets of 4-min high-intensity cycling followed by 4-min moderate-intensity cycling. After a 10-min warm-up, participants progress to moderate intensity before the first set of HIIT. High intensity is prescribed as 80–85% HRR or RPE 15–16 for the first 8 weeks and increased to 80–90% HRR or RPE 15–17 after week 8. Following the HITT session, a 10-min cool-down period is conducted.

CARE. CARE includes 20-min resistance exercise followed by 30-min cycling. Resistance exercises target six major muscle groups (chest press, shoulder press, squats, rows, leg press, calf raises), are performed on exercise machines, and are adapted for any mobility or musculoskeletal issues reported by participants. Intensity is based on estimated one-repetition maximal strength (1RM) and progress following guidelines for older adults [24]. It starts with 2 sets of 10–12 repetitions at moderate intensity (50–60% 1RM, 9–11 RPE) and progressively increases to 70–85% 1RM or 13–16 RPE by week 7. Rest intervals are 1–2 min between sets. Cycling intensity is 65–75% HRR or RPE 12–14, like exercise prescription used during the MICT.

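### H2a ranks HIIT and CARE (3-month non-responders only) against MICT only (responders only), so exercise type is aliased with response; only the HIIT versus CARE leg is randomised

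*Protocol article*

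**What the plan says.** Under Objectives {7}, Aim II seeks the best exercise for aerobic fitness. Its first hypothesis reads: "H2a: MICT + HIIT improves aerobic fitness the most, followed by MICT + CARE, then MICT only, and then stretching". Statistical methods {20a} gives the analysis: "To address H2a, we will estimate contrasts corresponding to a monotonic ordering of the means", where "mean aerobic fitness at 6 months is the highest in the MICT + HIIT group, followed by MICT + CARE, then MICT only, and then stretching".

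Membership of these groups is set in section {11b}: "Non-responders are re-randomized 1:1 to HIIT or CARE for 3 months", while "Responders continue MICT for 3 more months". Trial design {8} agrees. The first-choice non-response rule is a VO2peak gain below 5% at 3 months, so the variable that sorts people into groups is the one H2a compares at 6 months.

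Sample size {14} powers H2a on the same four groups and claims at least 80%. It takes HIIT-versus-CARE and HIIT-versus-MICT differences of d = 0.25-0.35 and MICT-only-versus-stretching differences of d = 0.40-0.55. No section redefines the groups as treatment strategies embedded in the SMART, and none describes weighting. Adjustment for 3-month VO2peak is stated for H2b only.

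**The concern.** A ranking of exercises needs groups that differ by exercise. Here they differ by exercise and by who responded. No non-responder stays on MICT and no responder receives HIIT or CARE, so no randomisation identifies HIIT or CARE against MICT only, and covariate adjustment cannot supply the missing cells. The comparisons of each aerobic subgroup with stretching also set a group selected after randomisation against an unselected arm.

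The trial could report HIIT as no better than continued MICT, or worse, when it is better for those who received it. The reverse error is also possible. If the ordering is tested with one trend contrast, a significant result may reflect only exercise versus stretching, which H1a already tests. Aim II is what the second randomisation was built to answer.

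**Working it through.** **1. Who is in each H2a group**

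| H2a group | 3-month status | How formed |
|---|---|---|
| MICT+HIIT | non-responders only | re-randomised 1:1 |
| MICT+CARE | non-responders only | re-randomised 1:1 |
| MICT only | responders only | not randomised at 3 months |
| Stretching | unselected | first randomisation |

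The aliasing follows from this table and needs no assumption. Only its size does.

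**2. The plan's own power figure.** Inputs from Sample size {14}: 60 aerobic and 29 control completers, and 13 each in HIIT and CARE, leaving 60 - 26 = 34 on MICT only. Take a linear contrast (-3, -1, 1, 3) over stretching, MICT only, CARE, HIIT. Its standard error in SD units is √(9/29 + 1/34 + 1/13 + 9/13) = √1.109 = 1.053.

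- Adjacent steps of 0.25 with MICT minus stretching 0.40: means 0, 0.40, 0.65, 0.90. Non-centrality (-0.40 + 0.65 + 2.70)/1.053 = 2.80, power 79%.
- Adjacent steps of 0.35 with 0.55: (-0.55 + 0.90 + 3.75)/1.053 = 3.89, power 97%.
- With baseline adjustment at r = 0.50 (divide the SD by √0.75 = 0.866 of its value, that is, use residual SD 0.866): 89-99%.

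The stated figure is therefore reachable if 0.25-0.35 is the step between adjacent groups. The seven scenarios, the sidedness and the contrast weights are not printed, so it cannot be reproduced uniquely.

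**3. Bias from selection alone.** Inputs: SD 4.8 and pre-post r = 0.50 from {14}. Assumed: baseline mean 16-20, mean MICT gain 1.5-3.12 mL/kg/min, and 0-3, 3-6 and 0-6 month correlations of (0.5, 0.5, 0.5), (0.5, 0.8, 0.5) or (0.7, 0.85, 0.7). Non-response means Y3 < 1.05·Y0. There is no second-stage effect.

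Unadjusted, with D = Y3 - 1.05·Y0 and p the non-response proportion, responders minus non-responders at 6 months, in SD units, is

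(r36 - 1.05·r06)/√(1 + 1.05² - 2.1·r03) × φ(k)/[p(1 - p)], with p = Φ(k).

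For baseline 16 and gain 1.5: D has mean 17.5 - 16.8 = 0.7 and SD 4.8 × 1.026 = 4.92, so k = -0.142, p = 0.44 and the last factor is 1.60.

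- Correlations (0.5, 0.8, 0.5): 0.275/1.026 × 1.60 = 0.43.
- Correlations (0.5, 0.5, 0.5): -0.025/1.026 × 1.60 = -0.04.

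The sign thus depends on whether 6-month fitness tracks the 3-month value more closely than baseline. Simulating the whole grid:

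| HIIT or CARE minus MICT only | SD units | mL/kg/min (× 4.8) |
|---|---|---|
| Baseline-adjusted | -0.47 to -1.06 | -2.3 to -5.1 |
| Unadjusted | about +0.04 to -0.44 | +0.2 to -2.1 |
| Planned HIIT minus MICT | +0.25 to +0.35 | +1.2 to +1.7 |

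A second grid (baseline 18-20, correlations 0.5-0.9) gave -0.41 to -0.96 adjusted and -0.44 to +0.11 unadjusted.

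**4. With a real benefit.** Simulated trials of 60 and 29, baseline 20, gain 0.475 SD, true HIIT +0.30 and CARE +0.15 SD over continued MICT. The adjusted HIIT-minus-MICT-only estimate averages -0.13 to -0.69 SD, and the hypothesised order of adjusted means appears in 0-5% of trials. Unadjusted, the estimate averages -0.14 to +0.41 SD and the order appears in 5-39%.

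**5. What one significant contrast would show.** Set all three exercise groups equally d above stretching. The linear non-centrality is 3d/1.053, which is 1.14 at d = 0.40 and 1.57 at d = 0.55. Across linear and maximin contrasts, unadjusted and adjusted, two-sided rejection is 20-46%, although no exercise beats another. With selection built in and no second-stage effect, the unadjusted rate was 7-31%.

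**The case against.** The strongest reply is that part of Aim II is sound. H2b compares HIIT with CARE by the second randomisation, adjusting for 3-month VO2peak, and the HIIT-CARE leg of H2a is randomised too. H1a compares the first-stage arms and is untouched. All of this stands. A reader might infer that the randomised HIIT-CARE comparison goes unanalysed for this aim. It does not: it is analysed as a binary response. What is not described is that comparison on continuous VO2peak, or any comparison of embedded strategies.

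The bias size can also be challenged. Baseline adjustment is stated for H1a, not for H2a, and without it the bias can be near zero or slightly positive. So it is not established that selection always lifts the MICT-only mean. That limits the size, not the aliasing.

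The rejection rates assume one trend contrast, whereas {20a} speaks of contrasts in the plural and distinguishes them from a linear trend. The rate is therefore conditional. Using H1a's d = 0.65 would raise it to 45-59%, but H2a's own MICT-versus-stretching effects are 0.40-0.55.

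Two further inferences are unsupported. The claim of at least 80% power is not shown to be wrong (step 2). Nor does a participant without a 3-month classification contradict "The ITT population will be defined as all randomized participants": section {11b} has a three-level fallback, and {20a} and {20c} plan multiple imputation.

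**Conclusion.** The concern holds for the MICT-only position in H2a and for the subgroup comparisons with stretching. As written, the ordering cannot attribute a difference between HIIT or CARE and MICT only to the exercise. HIIT versus CARE remains a valid randomised comparison among non-responders.

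That conclusion rests on the design alone. The size rests on the assumed baseline mean, gain and correlations. Under them the baseline-adjusted bias is larger than the planned effect and opposite in sign throughout. The unadjusted bias runs from negligible to somewhat larger than the planned effect. The finding does not extend to the stated power, to H2b or to the definition of the ITT population.

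**What to change.** 1. Restate H2a as an ordering of randomised strategies: MICT then HIIT if non-response > MICT then CARE if non-response > stretching. Estimate it by weighted-and-replicated regression with robust standard errors, responders contributing to both aerobic strategies. Weights are inverse assignment probabilities: responders 1/(2/3) = 1.5; re-randomised 1/(2/3 × 1/2) = 3; stretching 1/(1/3) = 3. Handle missing 3-month response with the multiple imputation already planned.
2. Report pairwise estimates with intervals beside the ordering.
3. Add HIIT versus CARE among re-randomised non-responders on 6-month VO2peak, by ANCOVA on baseline and 3-month VO2peak and age stratum, as an estimate with its interval and not as a confirmatory test.
4. Report MICT-only responders descriptively and take them out of the tested ordering.
5. Re-run and restate the H2a power on the new contrasts.

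The cost is wording and a new simulation, with no new data; recruitment is expected to run to March 2027, so the change can still be pre-specified. The MICT-only rank is given up, and shared responders dilute the contrast between the two aerobic strategies. HIIT versus CARE is weakly powered: with 13 per arm (normal approximation) the detectable difference at 80% power is (1.96 + 0.84) × √(2/13) = 1.10 SD, or 1.10 × 0.866 = 0.95 SD with baseline adjustment at r = 0.5. Power at d = 0.25-0.35 is 9-14% unadjusted and 11-18% adjusted. The protocol should say so.

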### Methods for additional analyses (e.g., subgroup analyses) {20b}

We collect three sets of biological variables: demographics (age, sex, race/ethnicity); *APOE* genotype; and MRI/blood biomarkers. MRI/blood biomarkers are study outcomes. We will treat demographics and *APOE* genotype as covariates in our main analyses and will conduct exploratory analyses to examine how these variables moderate treatment effects.

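### H2a is worded as improvement but tested on mean 6-month fitness with no fitness covariate named; adjust the randomised contrasts and label the steps against MICT only as descriptive

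*Protocol article*

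**What the plan says.** Objectives {7} sets Aim II as: "Determine the best exercise to improve aerobic fitness and reduce aerobic fitness non-responses over 6 months". Under it, H2a reads: "MICT + HIIT improves aerobic fitness the most, followed by MICT + CARE, then MICT only, and then stretching". Both are statements about gain from a starting point.

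Statistical methods {20a} tests H2a by contrasts for a monotonic ordering in which "mean aerobic fitness at 6 months is the highest in the MICT + HIIT group", followed by CARE, MICT only and stretching. That is a level at one visit.

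The neighbouring analyses each name a fitness covariate. H1a is fitted "adjusting for baseline aerobic fitness or WMHv and potentially relevant covariates", H1b is said to parallel H1a, and H2b is fitted "adjusting for 3-month VO_2peak". For covariates in general, the section on additional analyses {20b} says: "We will treat demographics and *APOE* genotype as covariates in our main analyses". It does not list baseline fitness.

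Under {11b}, the first-ranked criterion for non-response at 3 months is "< 5% increase in VO_2peak". Non-responders are re-randomised to HIIT or CARE, and responders stay on MICT.

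**The concern.** In a comparison of randomised groups, a difference in 6-month level and a difference in change have the same expectation, so the mismatch in wording costs only precision. H2a is not wholly such a comparison. Of its three adjacent steps, only HIIT versus CARE is randomised. CARE versus MICT only compares non-responders with responders. MICT only versus stretching compares responders with an unselected arm.

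Sorting people on change from baseline also sorts them on baseline: a high first test makes a gain of 5% less likely. The HIIT and CARE groups would therefore tend to start higher than MICT only, and level and change then answer different questions. If the plan does not fix which one H2a concerns, the ordering could be reported as supported on one scale and refuted on the other. The randomised step, which has few participants, would also give up precision that costs nothing to obtain.

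**Working it through.** **Inputs from Sample size {14}.** VO2peak SD 4.8; pre-post r 0.50; meaningful difference 3.12; 60 versus 29 completers at 6 months; 13 per arm for HIIT versus CARE; H2a steps of d = 0.25–0.35, which is 0.25 × 4.8 = 1.20 to 0.35 × 4.8 = 1.68 mL/kg/min.

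**The plan's own figure.** 3.12 / 4.8 = 0.65. With 60 versus 29 and two-sided 0.05 (sidedness is not stated), power is 81.1% by noncentral t and 82.0% by the normal approximation, against the stated 80%. The SD and effect size are therefore usable. The simulated H2a power cannot be reproduced, because its group sizes and seven scenarios are not given.

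**Randomised step, HIIT versus CARE.**
- Unadjusted: SE = 4.8 × √(2/13) = 1.88.
- Adjusted for baseline: 1.88 × √(1 − 0.50²) = 1.63, which is 13% lower.
- Adjusted for baseline and 3-month VO2peak, with r the correlation of baseline with each later visit and s the 3-to-6-month correlation: R² = (r² + s² − 2r²s) / (1 − r²).
  - r = s = 0.50: R² = (0.25 + 0.25 − 0.25) / 0.75 = 0.333; SE = 1.88 × √0.667 = 1.54, which is 18% lower.
  - s = 0.7 (assumed): R² = (0.25 + 0.49 − 0.35) / 0.75 = 0.52; SE = 1.30.
  - s = 0.8 (assumed): R² = (0.25 + 0.64 − 0.40) / 0.75 = 0.653; SE = 1.11.

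These formulas ignore selection and the small loss of degrees of freedom. A simulation restricted to non-responders at r = s = 0.50 gave 1.88, 1.58 and 1.54, so selection changes little.

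**Steps against MICT only.** Trivariate normal VO2peak at 0, 3 and 6 months was simulated with SD 4.8 throughout. Assumed, not in the document: normality, equal SDs, baseline mean 18, mean gain 1.7, and no second-stage treatment difference. The 5% rule then gives 44% non-responders, close to the plan's implied 26 of 60 (43%). Non-responders minus responders, mL/kg/min:

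| Baseline r | 3-to-6-month r | Baseline | 6-month level | Change | Baseline-adjusted |
|---|---|---|---|---|---|
| 0.50 | 0.50 | +4.0 | +0.1 | -3.9 | -2.3 |
| 0.50 | 0.70 | +4.0 | -1.4 | -5.4 | -4.1 |
| 0.50 | 0.80 | +4.0 | -2.1 | -6.1 | -5.0 |
| 0.70 | 0.70 | +3.3 | +0.3 | -3.0 | -2.3 |

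In each row, level minus change equals the baseline gap. Across assumed baseline means of 16–22 and gains of 1–3.12, that gap is 3.8–4.2 at r 0.50 and falls to 2.3–2.8 at r 0.9. With follow-up SD 10–30% larger it is 3.5–2.5 at r 0.50.

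**Can the order reverse?** Add the planned 1.20–1.68 to the first row. Level becomes +1.3 to +1.8 (HIIT above MICT only) and change becomes -2.7 to -2.2 (HIIT below). With baseline r 0.50, reversal is present at a 3-to-6-month correlation of 0.5–0.6, borderline at 0.7 and absent at 0.8–0.9. With all correlations equal at 0.7 it is present again: +1.5 to +1.9 against -1.8 to -1.3.

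**The case against.** The article never says that the H2a means are unadjusted. H1a is itself framed as change from baseline and then fitted as a 6-month outcome with a baseline covariate, so a mean at 6 months could be an adjusted mean. A condensed article may leave the covariates of one contrast to the analysis plan. This stands in part: absence of adjustment is an inference. It is a fair one, because every other hypothesis about fitness names its covariate and H2a has its own paragraph that names none. The difference between improvement and level, by contrast, is in the text.

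A reader might go further and infer that non-responders start about 4 mL/kg/min higher, that the level test will therefore mis-order the groups, and that baseline adjustment puts this right. The document supports none of these as fact. It gives no baseline value by response status. The gap is an assumption-based range of about 2.3–4.2, and reversal depends on correlations that the plan does not state. Baseline adjustment can also make matters worse. With no true treatment difference and r 0.50, it moves the contrast from between +0.1 and -2.1 on level to between -2.3 and -5.0, and it does not reproduce the change contrast either. In that model everyone has the same expected gain, so the deficit on change comes from sorting on response and does not show poorer training.

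**Conclusion.** The point holds in limited form. The hypothesis and its test name different quantities, and H2a alone among the fitness analyses names no fitness covariate.

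For HIIT versus CARE this is a matter of precision. The saving is 13–18% of the standard error at the plan's SD and r, equivalent at the upper end to 13 / 0.667 = 19.5 per arm unadjusted. It is larger if the 3-to-6-month correlation is 0.7–0.8 (SE about 1.1–1.3).

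For the steps against MICT only, the three ways of writing the contrast differ by several mL/kg/min with no treatment difference at all, which exceeds the planned steps of 1.20–1.68. That size rests on the assumed normality, equal SDs, baseline mean and gain. The mechanism does not, because it follows from forming groups on 3-month response. No choice among level, change and baseline-adjusted level makes those steps a treatment comparison.

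**What to change.** In Statistical methods {20a}, under H2a:

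1. State that the randomised contrasts are adjusted for fitness: baseline VO2peak for the whole arm starting on MICT versus stretching (the same model as H1a), and baseline plus 3-month VO2peak for HIIT versus CARE. For these contrasts the adjusted level difference also addresses improvement, so the test matches the Objectives.
2. State that the steps involving MICT only, on either side, compare groups formed by 3-month response, and are non-randomised and descriptive. Do not offer baseline adjustment as their remedy. If they are reported, name the scale in advance.

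The cost is two or three sentences and no new data, since screening fitness already serves as month 0 and VO2peak is measured at 3 months. The article gives recruitment as running to March 2027 with no interim analysis, so this can be settled before any comparison is made. The real price is that the full four-group ordering can no longer be presented as a randomised test of which exercise is best.
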